## Introduction

Severe complications of postacute COVID-19 infection like thrombosis, respiratory failure, and cardiac and vascular damage increase the likelihood of future morbidity and mortality in recovered patients. In one study of individuals who had been hospitalized with COVID-19, nearly a third (14,060/47,780, 29.4%) of individuals who were discharged from the hospital after acute COVID-19 were readmitted, and more than 1 in 10 (5875/47,780, 12.3%) died over a follow-up period of 140 days after discharge [1]. These events occurred at rates 4 and 8 times greater, respectively, than in the matched control group from the general population. In another study, the 6-month incidence of a new hospitalization among patients previously hospitalized with COVID-19 was found to be 29.8% [2]. SARS-CoV-2 infection can also lead to postacute development of substantial cardiac cellular abnormalities and cardiovascular clinical sequelae, including dysrhythmias, ischemic heart disease, heart failure, pericarditis, myocarditis, and thromboembolic disease [3]. Glycometabolic abnormalities are also evident in many survivors of acute COVID-19 and, in some cases, manifest as overt new-onset diabetes mellitus [4].

Risks of complications are higher among patients with comorbidities like congestive heart failure, chronic obstructive pulmonary disease, asthma, chronic kidney disease, diabetes, and hypertension [1,5,6]. Thus, although the current rate of new COVID-19 infection has dropped, the risk of morbidity, mortality, and organ dysfunction among the survivors of COVID-19 infection is high, especially among those with preexisting illnesses. Compelling evidence suggests that the pandemic may lead to new-onset kidney disease (and other noncommunicable chronic diseases including diabetes, cardiovascular disease, and neurological disease) in the millions. Given the scale and the chronic nature of several of its sequelae, post–COVID-19 condition (also known as “long COVID” or “postacute sequelae of COVID-19”) will reverberate with us for decades and will have broad and deep social and economic impact long after the COVID-19 pandemic abates [7]. Thus, it would be appropriate to infer that the next wave related to COVID-19 may not necessarily be a new strain but rather the surge of hospitalizations due to postacute complications. Developing strategies to prevent decompensation among high-risk survivors of COVID-19 has emerged as an unmet need.

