### Sample Size

To develop the AIDI algorithm, the study will collect longitudinal parameters that lead up to a DE with the MouthLab device. Because the actual multiparametric changes are unknown and are, in fact, the outcome of the study, the study aims to obtain as much data as possible from those who experience a DE. For this study, we estimate that 100 individual DEs would be sufficient to create a statistical algorithm to predict decompensation. The ultimate goal is to have the algorithm produce no false negatives (ie, if someone is at risk of decompensation while the algorithm says that they are not) and less than 10% false positives (ie, if someone is *not* at risk of decompensation while the algorithm says they are). That is, we do not want to miss any DEs at the cost of having some nonevents classified as being risky.

Al-Aly Z et al [11] observed that the risk and associated burden of pulmonary and extrapulmonary manifestations increase across the disease spectrum of acute COVID-19 infection (from nonhospitalized individuals to hospitalized individuals and then to those admitted to intensive care). The study implemented a comparative approach to examining postacute sequelae in individuals who are hospitalized with COVID-19 versus individuals with seasonal influenza (using a high-dimensional approach and through examination of prespecified outcomes). Results suggested that there is a substantially higher burden of a broad array of postacute sequelae in the individuals who are hospitalized with COVID-19, which provides features that differentiate post–COVID-19 condition (both in the magnitude of risk and the breadth of organ involvement) from postinfluenza viral syndrome [11]. A study by Mainous et al [2] demonstrated a hospitalization rate of 29.8% among survivors of “severe COVID-19.” Given that the AIDI study has defined “decompensation” more broadly than hospitalization alone, we anticipate higher decompensation rates among our study population. Conservatively estimating 1 DE per any participant, with an event rate of 60%, we would need 168 participants to complete the study in order to capture 100 DEs. Since we anticipate up to 15% dropout, we will aim to recruit 200 participants.

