### Evaluation of DEs

Data on outcomes (DEs) will be collected at the end of the data collection period via the CDW, records obtained from non-VA hospitalizations and ED visits, and monthly and end-of-study surveys.

A DE is defined as a complication related to organ dysfunction induced by SARS-CoV-19 that establishes the need for a change in treatment or intervention. To identify these events, we will first identify all new diagnoses and treatments, including medications, health care visits, and changes in level of service (eg, outpatient, inpatient, and hospital at home), for each patient during the study period using national CDW data. The data reviewed will be limited to those linked to relevant service types (eg, emergency care, urgent care, primary care, cardiology, and pulmonology). A study staff member will review these outcomes with guidance from the principal investigator or other team member with medical training to establish which are highly likely, somewhat likely, and not likely to be related to COVID-19. The full set of outcomes (Table 3) will be used as one outcome in one approach to the development of the predictive algorithm, and the subsets of highly likely and somewhat likely DEs will be used in a second approach to development.

**Table 3 table3:** Study outcomes.

Outcomes		Instrument or measure

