**Primary outcomes**		
	All-cause, higher-level health care use (hospitalization, ED^a^, or urgent care visits within the VA^b^ system)	Participant self-reporting, confirmed through EMRs^c^
	All-cause health care use (within and outside the VA system)	Participant self-reporting, confirmed through record requests and EMRs
	Highly likely COVID-19–related health care use	As evaluated by the PI^d^ and subinvestigators
	Highly likely and somewhat likely COVID-19–related health care use	As evaluated by the PI and subinvestigators

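### Table 3 confines all-cause higher-level care to the VA and conflicts with the text on how events are found, and no outcome includes death, so some decompensations are labelled as non-events

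*Protocol article*

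**What the plan says.** Table 3 of the protocol article lists four primary outcomes. The first is all-cause higher-level use: hospitalization, ED "or urgent care visits within the VA" system. Its stated measure is "Participant self-reporting, confirmed through EMRs". The second is all-cause health care use inside and outside the VA, again from self-report but confirmed through record requests as well as EMRs. The third and fourth are COVID-19-related use, graded by the investigators, with no VA limit.

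The section Evaluation of DEs describes the sources differently. Outcome data come from the VA Corporate Data Warehouse (CDW), "records obtained from non-VA hospitalizations and ED visits", and surveys, and the first step is to identify all new diagnoses, treatments and visits for each patient from national CDW data. One development approach uses the whole of Table 3 as a single outcome. A second uses the events graded highly or somewhat likely to be COVID-19-related.

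The same section defines a DE as a SARS-CoV-2-related complication "that establishes the need for a change in treatment or intervention". The Introduction and Study Timeline give the components as an ED visit, a hospitalization or escalated care. None of these places, nor Table 3, names death. The Introduction does cite a cohort in which 12.3% "died over a follow-up period of 140 days after discharge". Sample Size sets an ultimate goal of no false negatives.

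**The concern.** The outcome label is the reference against which every alert is judged, and it is also what the model learns from. If a real deterioration is labelled a non-event, a correct alert before it becomes a false positive, and the deteriorating readings become training examples of stability. Missing an event that the label does not recognise costs nothing in the reported performance, so the false-negative count is blind to it.

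Three features of the definitions can produce such labels: the VA limit on the first primary outcome, the dependence on self-report in Table 3, and the absence of death. Non-VA care is a realistic route. Recruitment is national, procedures are fully remote, and Data Blinding states that participants may seek any level of care. Self-report is most likely to fail in participants who become very ill, leave the study or die, which are the cases that the index is meant to detect.

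**Working it through.** **1. The plan's own figures.** Sample Size states "we estimate that 100 individual DEs would be sufficient to create a statistical algorithm to predict decompensation" and "we would need 168 participants to complete the study in order to capture 100 DEs", at a 60% event rate and one DE per participant, with 200 recruited for up to 15% dropout.

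- Completers: 100 / 0.60 = 166.7, so 167, against 168 stated.
- Recruited: 168 / 0.85 = 197.6, so 198, against 200 stated.
- Expected DEs: 168 × 0.60 = 100.8.

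These agree to rounding. The count assumes that DEs which occur are recorded as DEs.

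**2. The primary outcomes side by side.**

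| Table 3 row | Non-VA care counted? | Restricted to higher-level care? | All-cause? |
|---|---|---|---|
| 1 | No | Yes | Yes |
| 2 | Yes | No | Yes |
| 3 and 4 | No VA limit stated | No | No (COVID-19-related) |

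No row combines all-cause, higher-level and any provider. Pooling the whole table brings non-VA admissions back through row 2, but together with every other use that row 2 counts; Evaluation of DEs lists primary care among the relevant service types. One could read the VA limit in row 1 as applying to urgent care only. The absence of record requests from row 1's measure, and the contrast with row 2, make the wider limit the natural reading.

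**3. Possible size for row 1 evaluated alone.** Let m be the share of correct alerts that precede an event treated only outside the VA. The documents give no value, so m is an assumption. The abstract's target for positive predictive value (PPV) is above 70%.

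Measured PPV = 0.70 × (1 − m):

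- m = 0.10: 0.63
- m = 0.20: 0.56
- m = 0.30: 0.49
- m = 0.40: 0.42

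For a rough count, apply the 29.8% hospitalization rate in Sample Size to 168 completers: 0.298 × 168 = 50. If m is also the non-VA share of these, 5, 10, 15 and 20 admissions become non-events under row 1. They are not lost from the study, because row 2 still counts them.

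**4. How events are found.** Take a participant who stops answering surveys and later has a VA admission. Under Table 3's measure, no self-report exists to confirm, so there is no case. Under Evaluation of DEs, the CDW search finds it. The dropout allowance is 0.15 × 200 = 30 participants, which indicates how many could fall under diverging rules. For non-VA care the dependence on reporting is real under both texts: Safety Monitoring has participants report care in monthly surveys and sign a release if needed.

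**5. Death.** The cited mortality is 5875 / 47,780 = 12.3%. Applied to 200 participants it would give 24.6 deaths, but that is not the expected number. It covers 140 days (about four and a half months) from discharge, and participants enrol 3-6 months after hospitalization. With assumed mortality of 1%, 2% or 5% over follow-up, total deaths are 2, 4 or 10. Only deaths with no counted care are affected. If that is 25% to 100% of deaths (also assumed), the numbers are 0.5 to 2, 1 to 4 and 2.5 to 10.

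Outcome Modeling predicts a DE within a window τ. A death after an earlier, unconnected visit can therefore also lack an event label in its own window.

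**The case against.** The strongest reply is that non-VA care is already counted. Row 2 covers it, rows 3 and 4 carry no VA limit, and neither development approach in Evaluation of DEs is described as using row 1 alone. This stands to a large extent. A reader might infer that non-VA admissions are lost from the study, or that the model will generally be trained on them as healthy examples; the documents do not support either. The PPV figures above apply only where row 1 is evaluated by itself. The reply leaves untouched that row 1 is a named primary outcome and that no other row measures all-cause acute care.

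A second reply is that VA events do not depend on self-report, because the CDW is searched for each patient. That is what Evaluation of DEs says, so a reader should not infer that unreported VA events will necessarily be missed. It is not what Table 3 says, and the two remain to be reconciled.

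On death, one can say that most deaths follow an ED visit or admission, that the 12.3% largely predates enrolment, that Limitations expects the sickest patients not to enrol, and that censoring at death may be set out in a full protocol or analysis plan that is not shown. All of this reduces the likely number, and no claim is made that a censoring rule is missing. But the article itself fixes what a DE is and what the outcomes are, and a death without counted care meets none of them.

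**Conclusion.** The point holds in three limited parts. The first primary outcome excludes non-VA higher-level care, and no other outcome supplies that measure. Table 3 and Evaluation of DEs give conflicting rules for finding events. Death is outside every outcome as written, which sits badly with the goal of no false negatives.

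The direction of the first and third effects is clear: some correct alerts count as false positives and some pre-event windows as negatives. The size is unknown. The PPV range of 63% to 42% rests on an assumed 10% to 40% non-VA share, equal alerting for VA and non-VA events, and row 1 used alone. The range of 0.5 to 10 mislabelled deaths rests on assumed mortality of 1% to 5% and an assumed share without counted care. A reader might take 12.3% as the mortality to expect; the enrolment window rules that out. The sample-size arithmetic is not in question.

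**What to change.** - Widen the first primary outcome to hospitalization, ED or urgent care within or outside the VA system, and add record requests to its measure. The VA-only version can be kept as a sensitivity analysis.
- Reconcile Table 3 with Evaluation of DEs: take VA events from the CDW for every participant regardless of self-report, and use self-report to locate non-VA events.
- Add death to the all-cause outcomes, and grade it on the existing relatedness scale for the COVID-19-related outcomes. Amend the DE definition to match.

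The cost is edits to Table 3 and the DE definition. The CDW extract and non-VA records are already planned, and outcomes are collected at the end of the data collection period. The article reports 204 patients already enrolled, so the change should be recorded and dated before labels are finalised and performance is examined. Two weaknesses remain: non-VA events may be dated less precisely, which matters for short τ, and finding them still depends partly on participants reporting them.

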**Secondary outcomes**		
	Highly likely and somewhat likely COVID-19–related health care use	As evaluated by the PI and subinvestigators
	Highly likely COVID-19–related diagnoses, treatment, use, and medication	As evaluated by the PI and subinvestigators and confirmed in EMRs

^a^ED: emergency department.

^b^VA: Department of Veteran Affairs.

^c^EMR: electronic medical record.

^d^PI: principal investigator.

### Data Blinding

Participants and physicians are blinded to the data from the MouthLab device. Participants will be informed that they are not restricted from seeking any level of care. There will be no medical intervention provided during or after the study as a consequence of any unfavorable trends in the MouthLab data, as these data are not being surveilled during the study.

### Participant Data Protection

The confidentiality of participants will be maintained throughout the study. All participants will be assigned a unique subject ID by the data analyst. The crosswalk that matches the participant ID to the participant’s name will be secured behind the VA firewall. Any data that may be published in abstracts and scientific journals or presented at medical meetings will reference the unique participant ID or will be aggregated, so to not reveal the participant’s identity. Patient identifiable information such as name, address, email address, and phone number will only be used to support device shipment and return–related activities. Participants’ unique identifiers, rather than personal information, will be connected to their device and survey data as well as any other data obtained from the electronic medical record. To protect participants’ privacy, the Aidar Connect dashboard will not collect any patient identifiable information during registration, and pairing of MouthLab devices will be performed against the participants’ IDs.

### Safety Monitoring

During the monthly health surveys sent via the VA Office of Research and Development Qualtrics platform, participants will report any potential adverse events (AEs) that are possibly related to their COVID-19 diagnosis, as well as to any hospitalizations or medical care use. Study coordinators will follow up with participants to gather more information and have participants sign a Release of Information if needed. The investigator or study coordinator will determine whether the AE or serious AE meets the criteria for reporting; submit to the sponsor and VA Central Institutional Review Board all associated information and documentation related to each AE or SAE; and execute corrective actions as necessary.

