One approach to the prevention of decompensation is to monitor for worsening in physiological parameters after hospital discharge. However, collecting such data longitudinally for prediction poses several challenges. First, only a limited number of parameters can be easily collected (eg, blood pressure, heart rate, oxygen saturation, etc), although additional parameters such as heart rate variability and lung function may provide additional prognostic data. Second, even if patients or families are able to collect these parameters longitudinally, there is no automated, validated method to analyze those data concurrently and provide a quantitative assessment of decompensation risk over time. These limitations hinder the sensitivity and thus the utility of current approaches to using physiologic parameters to predict decompensation risk among patients after COVID-19.

The overall objective of this study (trial registration: ClinicalTrials.gov NCT05220306) is to use a handheld, multisensor device—MouthLab, which measures 10 vital health parameters in 60 seconds—and a cloud-based proprietary engine to develop and validate the Aidar Decompensation Prediction Index (AIDI). MouthLab measures oral temperature, single-lead electrocardiogram, heart rate, breathing rate, heart rate variability, respiratory flow morphology, oxygen saturation, pulse rate, and basic lung function (forced expiratory volume in the first second and peak expiratory flow rate). The study will collect MouthLab data from patients previously hospitalized with COVID-19 (“severe COVID-19”) in order to identify decompensation predictor variables. These variables will be used to develop the AIDI to accurately predict decompensation events (DEs) related to post–COVID-19 condition. Index development will follow best practices in machine learning and algorithmic development, where the main outcome is any COVID-19–related event that leads to an emergency department (ED) visit, hospitalization, or the need for escalated care (new diagnosis or change in intervention to manage the chronic conditions). These DE cases will help inform the final set of predictor variables to develop the AIDI. In the future, early prediction and real-time risk triaging using the AIDI may support better clinical decision-making, thus preventing complications, controlling disease progression, and improving outcomes. The aim of this paper is to describe the protocol for this study to develop and validate the AIDI.

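### Safety Monitoring asks for adverse events linked to COVID-19 and for care use but never for events linked to MouthLab use, and lets reportability be decided without stated medical input

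*Protocol article*

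**What the plan says.** Safety Monitoring makes the monthly health survey the source of AE reports. In it "participants will report any potential adverse events (AEs) that are possibly related to their COVID-19 diagnosis", and the sentence goes on "as well as to any hospitalizations or medical care use". Then "Study coordinators will follow up with participants to gather more information", obtaining a signed release of records where needed.

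On the reporting decision the section says: "The investigator or study coordinator will determine whether the AE or serious AE meets the criteria for reporting". The same people are to "submit to the sponsor and VA Central Institutional Review Board all associated information and documentation related to each AE or SAE" and to carry out corrective actions.

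Other sections bear on this:
- Study Design requires MouthLab use twice daily. The Introduction lists forced expiratory volume and peak flow among the readings.
- Asthma, chronic obstructive pulmonary disease and heart failure are among the qualifying conditions.
- Table 2 places the MouthLab usability survey at study conclusion.
- Evaluation of DEs has a staff member grade how likely each outcome is to be related to COVID-19, "with guidance from the principal investigator or other team member with medical training".

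**The concern.** COVID-19 is the condition that brings people into this study; it is not something the study does to them. What the study does is ask them to use a device repeatedly and answer surveys. An AE question framed around COVID-19 asks about the disease and leaves out the procedure. It also makes the participant the first judge of causality. Under Evaluation of DEs the study itself uses three grades of likelihood and medical guidance to make that judgement.

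The second issue is who decides. As written, a coordinator may settle the reportability of an AE, including a serious one, with no medical input stated. At stake are the completeness of the record on how well repeated device use is tolerated and the soundness of reporting decisions in a cohort chosen for high risk. The predictive performance of the index is not at stake.

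**Working it through.** The point is textual and the plan gives no figure to reproduce, so the check sets the sections side by side.

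**1. What the AE sentence covers.** It has two limbs: events possibly related to COVID-19, and hospitalizations or care use. The grammar of the second limb is loose. On its natural reading, all hospitalizations and care use are reported whatever the cause. On its literal reading, it covers AEs related to such care. Neither reading names the device or study procedures.

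**2. Sort a device-related event by two questions: did it lead to care, and does the participant link it to COVID-19?**
- Care sought, linked or not: collected through the second limb on its natural reading. Table 3 also makes all-cause care use, inside and outside the VA, a primary outcome, confirmed from records.
- No care, linked to COVID-19: collected through the first limb.
- No care, not linked to COVID-19: solicited by neither limb.

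The gap is the last case only.

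**3. Does another described channel close it?**
- The monthly scales cover dyspnea and functional status. They could show a worsening but do not ask about device use.
- The usability survey comes once, at the end, and is not described as AE capture.
- Data Blinding says the MouthLab data are not surveilled during the study.
- Strengths mentions stepping in when data are absent or a participant is not complying. Such a contact might bring a complaint to light by chance, but it is not described as safety collection.

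None of these solicits the event in question.

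**4. Who decides.** Safety Monitoring names the investigator or the coordinator, joined by an or, for AEs and SAEs alike, and states no medical input. Evaluation of DEs states medical guidance for outcome grading. That review cannot serve as a backstop for timely safety reporting, because the same section has outcome data collected at the end of the data collection period.

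**5. Exposure, for scale only.** Take 6 months as about 180 days (an assumption: 6 × 30), with all 200 planned participants fully adherent. Twice-daily use gives 200 × 2 × 180 = 72,000 sessions. The Abstract says daily; if that means once a day, the figure is 200 × 1 × 180 = 36,000. Both are upper figures, since the Sample Size section allows for up to 15% dropout. They count exposure. The documents give no rate of device-related events, so no count of missed events can be derived.

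**The case against.** The strongest reply has four parts.

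**The AE sentence is wider than its first half.** It also takes in hospitalizations and care use, and all-cause use is an outcome in its own right. This stands. A reader might infer that device harms go uncollected or that the study will have no device-safety record at all. The documents do not support that, because any harm leading to care is captured.

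**Screening-out of serious events is not shown.** A reader might infer that a coordinator will drop serious events unseen. The text does not go that far. The decision is made against reporting criteria, the investigator is a named alternative, and the section also has information on each AE or SAE sent to the sponsor and the VA Central Institutional Review Board. What remains is that the wording permits a coordinator to decide alone and states no medical input.

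**This is a condensed article.** Reporting criteria, device-event definitions, delegation of duties and the survey items may sit in the full protocol, and their absence here is no fault. That also stands. But the article does more than stay silent: it states the scope of what participants are asked and who may decide. A fuller document that asked about device events would have to widen that stated scope, and the two should then be reconciled.

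**Device safety is not a study aim.** Correct: the aim is to develop and validate the index, so the study cannot be faulted for failing to prove the device safe. Asking participants about the one procedure they repeat is ordinary safety capture whatever the aim. The article also looks ahead to home monitoring with the index.

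**Conclusion.** The point holds in a narrow form. Device-related events that lead to no care, and that the participant does not attribute to COVID-19, are not solicited by any channel the article describes. Separately, the reportability of AEs and SAEs may be decided without the medical guidance that the article states for outcome grading.

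This is a minor point on safety capture. It leaves sample size, outcomes, error rates and the planned analysis untouched. The session figures show how often the procedure is repeated and say nothing about how much harm occurs.

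The verdict rests on two assumptions: that the second limb of the AE sentence is read in its natural sense, and that the article states the survey's scope faithfully. If the literal reading were meant, the gap would be wider for self-reported AEs, though all-cause care use would still be collected as an outcome.

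**What to change.** In Safety Monitoring:

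1. Have the monthly survey ask for any new or worsened health problem regardless of suspected cause, and add one item on symptoms during or after MouthLab use. The study team, not the participant, then assesses relatedness to the device and to COVID-19. Keep the question on hospitalizations and care use as it is, because the monthly surveys also feed outcome ascertainment.
2. State that the coordinator collects and submits, and that a medically qualified investigator determines seriousness and reportability, in line with Evaluation of DEs.
3. If the full protocol already provides for either, bring the two texts into agreement.

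The cost is one or two items in an existing survey, a wording change, and some extra minor AE reports for the investigator to review. Because Results reports 204 patients already enrolled, the wording would change partway through data collection at best. The date of the change should be recorded, and AE counts from before and after it should not be read as comparable.
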